## Methods/Design

### Research design

This study is a PROBE (Prospective, Randomized, Open-label, Blinded-Endpoint) design clinical trial.

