### Sample size calculation

According to data reported by Marfella *et al*. [8], a total sample size of 20 patients (allowing for a dropout rate of 10%) should allow detection of a difference between groups with MAGE levels (mean ± SD) of 25.0 ± 16 mg/dl at week 12, assuming statistical power of 90%, and a significance level of 1% (two-sided, two-sample *t*-test).

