### Randomization

The randomization sequence will be generated by the R software (v2.12.1 Vienna, Austria, 2011), with a block size of five. Randomization to the metformin plus vildagliptin group (METV) or the metformin plus glibenclamide group (METG) will be performed by a researcher responsible only for this task, who will not participate in the recruitment, assessment, or intervention phases of the study.

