### Statistical analysis plan

Data will be analyzed using SPSS software (Statistical Package for Social Sciences; version 18.0 for Windows, SPSS Inc., Chicago, USA). The description of values will be expressed as mean ± SD. The statistical procedures used will be Student’s *t*-test for independent samples (intergroup analysis), paired *t*-test (intragroup analysis), and analysis of variance (ANOVA) for repeated measures to compare both groups at different times. A Pearson correlation will be performed between measures of glucose variability and 8-isoPGF2α/crn. The statistical power will be 90%, and the accepted level of significance will be *P* < 0.01.

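### A block size of five cannot be balanced between two arms, so the randomisation rule as stated does not ensure equal groups; the cost is small and the fix is simple

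*Protocol article*

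**What the plan says.** The Randomization section of the protocol article says that the sequence is "generated by the R software (v2.12.1 Vienna, Austria, 2011), with a block size of five". It names two groups, metformin plus vildagliptin (METV) and metformin plus glibenclamide (METG). It assigns the task to a researcher who has no part in recruitment, assessment or intervention.

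The Sample size calculation section gives "a total sample size of 20 patients", including a 10% allowance for dropout. The target is "a difference between groups with MAGE levels (mean ± SD) of 25.0 ± 16 mg/dl at week 12". The calculation is for an independent-samples *t*-test with 90% power at the two-sided 1% level. It gives no numbers per arm.

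The Research design section describes a "PROBE (Prospective, Randomized, Open-label, Blinded-Endpoint) design clinical trial". The Data collection section places randomisation on Day 3, after the baseline tests.

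No section gives an allocation ratio, the composition of a block, or a rule for setting one block against another.

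**The concern.** In a trial of 20 patients, permuted blocks serve mainly to keep the arms level. With two arms and 1:1 allocation, that works only if the block size is even. A block of five always leaves one arm a patient ahead, and the text does not say which arm, or whether a later block corrects it. Two programmers following the rule could produce lists with different expected arm sizes.

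At stake are a little precision in the primary comparison and a rule that can be carried out as written. A secondary matter is that a single block size is published for an open-label trial run in one laboratory, which helps anyone trying to guess the next allocation.

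**Working it through.** **Inputs.** From the protocol article: block size 5 and two arms (Randomization); total 20 with 10% dropout, two-sided 1%, 90% power, two-sample *t*-test (Sample size calculation). The article's 25.0 ± 16 mg/dl is read as a between-group difference of 25 with a common SD of 16; this is an assumption. Equal allocation is also an assumption, the usual default when only a total is given.

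**The plan's own figure.** The normal formula per arm is n = 2(z₁₋α/₂ + z₁₋β)²(SD/difference)².
- At two-sided 1% and 90% power: 2 × (2.576 + 1.282)² × (16/25)² = 12.2, so 13 per arm, 26 in total, and 26/0.9 → 29 with dropout. The exact *t*-test needs 14 per arm, 28 in total, 32 with dropout.
- At two-sided 5%: 2 × (1.960 + 1.282)² × (16/25)² = 8.6, so 9 per arm, 18 in total, and 18/0.9 = 20.

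The stated 20 therefore does not reproduce at the stated 1%. That is a separate and larger issue. Its only effect here is that the power figures below start from about 72%, not 90%.

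**Possible splits.** 20/5 = 4 full blocks, each giving METV two or three patients.
- Same arm always favoured: 4 × 3 = 12 against 4 × 2 = 8.
- Majority arm chosen at random in each block (assumed): 16 equally likely patterns.

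| Split (either way) | Patterns | Probability |
|---|---|---|
| 10:10 | 6 of 16 | 37.5% |
| 11:9 | 8 of 16 | 50% |
| 12:8 | 2 of 16 | 12.5% |

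- Two 3:2 blocks deliberately paired with two 2:3 blocks: exactly 10:10, but the text gives no such rule.

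**Effect on power.** Exact two-sample *t*-test: noncentrality = 25 / [16 × √(1/n₁ + 1/n₂)], with n₁ + n₂ − 2 degrees of freedom, two-sided 1%.

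| Split | √(1/n₁ + 1/n₂) | Noncentrality | Power |
|---|---|---|---|
| 10:10 | 0.4472 | 3.494 | 72.3% |
| 11:9 | 0.4495 | 3.476 | 71.8% |
| 12:8 | 0.4564 | 3.423 | 70.2% |
| 9:9 | 0.4714 | 3.315 | 65.3% |
| 10:8 | 0.4743 | 3.294 | 64.6% |
| 11:7 | 0.4835 | 3.232 | 62.5% |

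The worst case with all 20 patients costs 72.3 − 70.2 = 2.1 points, and the standard error rises by 0.4564/0.4472 − 1 = 2.1%. With 18 evaluable, 11:7 costs 65.3 − 62.5 = 2.8 points against 9:9. Averaged over the random composition, power at 20 is 0.375 × 72.3 + 0.5 × 71.8 + 0.125 × 70.2 = 71.8%, about half a point below 10:10.

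**Predictability.** If every block is 3:2 in the same direction and this is known, the fifth allocation always follows from the first four. If the majority arm is random, the first four stand at 2:2 in 3/5 = 60% of blocks, which leaves the fifth open, and at 3:1 in 40%, which settles it. In a known fixed block of four, the last allocation is always settled.

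**The case against.** A reader might infer that equal arms are impossible. The documents do not support that: it is true within each block, but four blocks can total 10:10 by chance or by pairing.

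A reader might also take the trial to be explicitly sized for equal groups. That is only the natural default, since the article gives a total and no ratio. As the article condenses a fuller protocol, the ratio and block composition may be set out there. Silence on those details alone would be no finding. What survives is that the article does state a block size, and the one it states does not fit two equal arms unless something further is added.

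Nor is balance lost altogether. After four blocks the imbalance cannot exceed 12:8, and under random composition it reaches that only 12.5% of the time. Simple randomisation of 20 patients gives 12:8 or worse about 50% of the time (binomial, 20 draws at 0.5). Dropout can unbalance the analysed groups under any block size. All of this stands, and it limits the severity.

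Finally, a reader might infer that concealment is compromised. The separate randomising researcher and the Day 3 timing both count against that. They do not stop staff in an open-label trial from seeing past allocations, so some scope for guessing remains, but the documents do not show that concealment fails. Moving to a fixed block of four would make guessing easier if the size were known.

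**Conclusion.** The point holds as one of specification and balance. A block size of five for two arms, with no ratio or pairing rule, does not ensure equal groups. Unequal arms result with certainty if one arm is always favoured, and with probability 62.5% if the majority arm is random in each block.

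The consequence is small: at most about 2 points of power with 20 patients and about 3 with 18 evaluable, with no bias from the imbalance itself. These figures rest on reading the target as a difference of 25 with SD 16, on 1:1 being intended, and, for the probabilities, on random block composition. The 11:7 figure also assumes that a 12:8 allocation loses one patient from each arm.

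It would be wrong to conclude that the block size explains the gap between about 72% and the claimed 90% power. That gap is present at 10:10 and comes from the total of 20. Severity is minor to moderate.

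**What to change.** State 1:1 allocation and replace the block size of five with even permuted blocks. Two blocks of four and two of six in random order total 2 × 4 + 2 × 6 = 20 and give exactly 10:10. Because the trial is open-label, keep the sizes from recruiting and assessing staff and out of public text until enrolment closes. Five fixed blocks of four would also give 10:10 but are the weaker choice, for the reason given above.

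If the list has not been used, the cost is one sentence and a regenerated list, with no extra patients. Whether that is so is unclear: Trial status says recruitment has not begun and gives April 2014 for enrolment, while the article is dated November 2014. If the list is in use, or an unequal ratio such as 3:2 was intended, leave it in place, report the actual ratio and block composition, and base the power statement on those arm sizes. If the total of 20 is revised, choose even block sizes that sum to the new total.

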### Data collection

Eligible patients will initially perform a maximum effort test, and 48 hours later, they will begin the study protocol, as follows:

Day 1: Begin 24-hour urinary collection, perform vascular Doppler ultrasound to evaluate endothelial function, and then insert glucose sensor subcutaneously to begin continuous glucose monitoring system (CGMS) evaluation.Day 2: End the 24-hour urinary collection, carry out the submaximal exercise test (with blood collection at baseline, 15, and 30 minutes into the session, and 60 minutes after recovery). Assess heart rate variability 10 minutes before and after the submaximal exercise test, and begin 24 h ambulatory blood pressure monitoring (ABPM).Day 3: Removal of the glucose sensor; end 24 h ABPM. Randomization.

This same protocol will be repeated at the end of the 12-week treatment with vildagliptin or glibenclamide.

The experimental sessions will occur at the Exercise Pathophysiology Research Laboratory, Hospital de Clínicas de Porto Alegre (LaFiEx-HCPA), maintaining the ambient temperature at between 20 and 22°C.Patients will be asked to follow their habitual diet during the 3 days of protocol. To carry out the submaximal exercise test they will go to LaFiEx-HCPA in a fasted state. Patients will record detailed food intake in diaries across the 3 days of CGMS use. The dietary assessment will be performed using the software DietWin (DietWin, Porto Alegre, Brazil). In addition, participants will be instructed to avoid intense activities and not to consume caffeinated beverages on the day before the dietary assessment, in order to exclude any residual effect before and after the effort test. The submaximal exercise test will occur after a standard breakfast (500 kcal; 60% carbohydrate, 30% fat and 10% protein). During the drug treatment period (12 weeks) patients will not follow any kind of physical exercise program. The flow diagram of the study design is shown in Figure 1.

**Figure 1 Fig1:**
[figure not shown]
**Flow diagram of the study design.** # The submaximal exercise test (SET) will occur on the day 2 of a 3-day period of tests. METV group: 12 week s of treatment with vildagliptin added to metformin; METG group: 12 weeks of treatment with glibenclamide added to metformin. *500 to 2000 mg/day according to tolerance; **50 mg twice daily; ***10 to 20 mg twice daily. ABPM: ambulatory blood pressure monitoring, CO: cardiac output, CGMS: continuous glucose monitoring system; BS: blood sample; HRV: heart rate variability, MET: maximal exercise test. †Metabolic evaluation: glucose, HbA1c, insulin, glucagon-like peptide 1 (GLP-1).

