**Methods/Design:**

This study is a PROBE (Prospective, Randomized, Open-label, Blinded-Endpoint) design clinical trial.

The estimated sample needed is 20 patients with T2DM. In addition to the routine treatment (metformin), patients will receive a second drug orally for 12 weeks: the METV group will receive metformin plus vildagliptin (50 mg twice daily), and the METG group will receive metformin plus glibenclamide (5 to 10 mg twice daily.). Before and after intervention, evaluation of glycemic variability, endothelial function, oxidative stress, and metabolic and cardiovascular response will be performed at rest, during and after a submaximal exercise test (30 minutes, with an intensity based at 10% under the heart rate at the second threshold).

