### Study intervention

The METV group will receive 50 mg of vildagliptin orally twice a day. The METG group will receive glibenclamide 5 mg orally once per day during the first week of the study, then in the second week, the dose will be increased to 10 mg a day (5 mg twice a day). The dose may be adjusted to reach a target pre-prandial capillary plasma glucose level of 70 to 130 mg/dl without frequent or severe hypoglycemia, up to the maximum dose allowed (20 mg a day). Patients will be instructed to measure capillary glycemia using a glucose monitor (Accu-Check Performa; Roche Diagnostics, Mannheim, Germany) twice a week and at any time if they believe they have symptoms of hypoglycemia. These measured values will be recorded at the follow-up visits or passed on to the researchers in a phone call when two consecutive values lower than 70 mg/dl occur. This procedure will be explained at the beginning of the study. Medication adjustments will be guided by the researcher coordinator ([name]). Drug accountability will be assessed at each follow-up visit.

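### The glibenclamide dose in the Figure 1 legend conflicts with the intervention section and the abstract; its upper end is twice the daily maximum stated in the text

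*Protocol article*

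**What the plan says.** The protocol article states the comparator dose in three places.

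- **Figure 1 legend.** Three starred footnotes give doses. The third reads "10 to 20 mg twice daily". The legend does not name the drug beside that footnote, and the figure image is not available here.
- **Study intervention section.** "The METG group will receive glibenclamide 5 mg orally once per day during the first week of the study". For the second week, "the dose will be increased to 10 mg a day (5 mg twice a day"). After that the dose may be adjusted towards a pre-prandial glucose target, provided hypoglycemia is neither frequent nor severe, "up to the maximum dose allowed (20 mg a day").
- **Abstract, Methods/Design.** "the METG group will receive metformin plus glibenclamide (5 to 10 mg twice daily").

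The Data collection section refers the reader to Figure 1 for the study design. The Study intervention section has the research coordinator guide medication adjustments.

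**The concern.** One document should not give two incompatible ranges for the same drug. The legend's range lies at or above the ceiling stated in the Study intervention section, and most of it lies strictly above.

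Two things are at stake.

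- **Safety, on the article's own terms.** The text makes glibenclamide adjustment conditional on avoiding frequent or severe hypoglycemia. Patients measure capillary glucose twice a week or when they suspect symptoms, and they do a submaximal exercise test at the end of the 12 weeks. A conflict over the maximum dose of that drug is more than cosmetic.
- **The description of the comparator.** Glibenclamide is the only comparator to vildagliptin. A reader of the whole article cannot tell which dose range was permitted in that arm.

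**Working it through.** **Step 1: which drug the third footnote belongs to.** The first footnote, 500 to 2000 mg a day according to tolerance, fits only metformin. The second, "50 mg twice daily", is the vildagliptin dose in both the abstract and the Study intervention section. Glibenclamide is the only study drug left. This is an inference by elimination, but no other assignment fits.

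**Step 2: convert each statement to a daily dose.** Daily dose = dose per intake × intakes per day.

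| Source | Per intake | Intakes per day | Daily dose |
|---|---|---|---|
| Study intervention, week 1 | 5 mg | 1 | 5 mg |
| Study intervention, week 2 | 5 mg | 2 | 5 × 2 = 10 mg |
| Study intervention, maximum | not given | not given | 20 mg |
| Abstract, lower end | 5 mg | 2 | 5 × 2 = 10 mg |
| Abstract, upper end | 10 mg | 2 | 10 × 2 = 20 mg |
| Figure 1 legend, lower end | 10 mg | 2 | 10 × 2 = 20 mg |
| Figure 1 legend, upper end | 20 mg | 2 | 20 × 2 = 40 mg |

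**Step 3: reproduce the article's own figures.** The abstract's upper end gives exactly the 20 mg daily maximum of the Study intervention section, and its lower end gives exactly the week 2 dose of 10 mg. These two sources therefore agree from week 2 onward. The abstract leaves out only the single week at 5 mg a day.

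**Step 4: compare with the stated maximum.** Ratio = daily dose ÷ 20 mg.

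- Abstract: 10 ÷ 20 = 0.5 to 20 ÷ 20 = 1.0.
- Figure 1 legend: 20 ÷ 20 = 1.0 to 40 ÷ 20 = 2.0.

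**Step 5: look for overlap.** The legend covers 20 to 40 mg a day. The other two sources, from week 2, cover 10 to 20 mg a day. The only common value is 20 mg a day. No reading of the words as printed makes 40 mg a day compatible with a maximum of 20 mg a day.

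**The case against.** The strongest reply is that this is one slip in a figure legend, and that the operative text is clear. The Study intervention section sets out the starting dose, the second-week dose, the maximum and a glucose target. It also requires a phone report after two consecutive values below 70 mg/dl, and one coordinator guides adjustments. The experimental sessions take place at a single laboratory. Nothing says that anyone doses from the figure.

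Much of this stands, and it rules out several stronger readings that a reader might infer.

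- **That there are three different regimens.** The abstract and the Study intervention section agree from week 2 onward, and leaving out a one-week starting step is ordinary condensation in an abstract. The conflict is between the legend and the other two.
- **That the legend is fourfold out.** The arithmetic 20 ÷ 5 = 4 sets the legend's lower end against a one-week starting dose. By the same method the abstract would be 10 ÷ 5 = 2 times out, although it agrees with the text. The like-for-like figure is 40 against 20 mg a day, a factor of two.
- **That staff would exceed the ceiling, or that patients were misdosed.** At its lower end the legend meets the ceiling; only doses above that conflict with it. With an explicit schedule in the text and coordinated adjustment, the supportable word is could. The article contains no evidence of misdosing.
- **That the variability result would refer to no identifiable dose.** The dose is individually adjusted, so no single dose was ever planned. Only the permitted range is uncertain.

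It may also be said that the legend's numbers, read per day instead of per intake, would match the abstract's daily range. That is a possible origin of the discrepancy, but the article does not say so, and a reviewer should not settle a maximum dose by guessing which text is the slip.

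What the reply does not do is remove the contradiction. The legend is intact, current text. Condensation can explain an omitted step but not a doubled upper limit, and no fuller protocol could make both statements true.

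**Conclusion.** The concern holds as an internal inconsistency. The legend's range of 20 to 40 mg a day runs from one to two times the stated maximum of 20 mg a day, and it meets the Study intervention section and the abstract only at that single value. The conclusion rests on one inference, that the third footnote is glibenclamide, which the other two footnotes make secure.

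It should be corrected without exception, because it concerns a stated maximum dose of a drug whose adjustment is limited by hypoglycemia, and because the correction is cheap. It is not a criticism of the choice of comparator or of the design. The sample size, power, significance level and analysis methods do not depend on it. Using the text's maximum as the reference for the ratios does not imply that the text is the correct source.

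**What to change.** Reconcile the Figure 1 legend with the Study intervention section and the abstract, so that the article carries one consistent statement of the glibenclamide dose and its maximum. The responsible clinician should confirm that statement against the ethics-approved protocol. This review does not say which of the conflicting figures should stand.

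Then check the site documents (dosing instructions, prescribing sheets, any copy of the flow diagram) for the same conflict. The Trial status section puts the start of enrolment in April 2014, and the article was published in November 2014, so treatment may already have begun. If it has, the check should also establish and record which regimen was used.

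The cost is a correction to a legend or to the text, plus a short document check. No analysis, sample size or visit schedule changes.

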### Study intervention

The METV group will receive 50 mg of vildagliptin orally twice a day. The METG group will receive glibenclamide 5 mg orally once per day during the first week of the study, then in the second week, the dose will be increased to 10 mg a day (5 mg twice a day). The dose may be adjusted to reach a target pre-prandial capillary plasma glucose level of 70 to 130 mg/dl without frequent or severe hypoglycemia, up to the maximum dose allowed (20 mg a day). Patients will be instructed to measure capillary glycemia using a glucose monitor (Accu-Check Performa; Roche Diagnostics, Mannheim, Germany) twice a week and at any time if they believe they have symptoms of hypoglycemia. These measured values will be recorded at the follow-up visits or passed on to the researchers in a phone call when two consecutive values lower than 70 mg/dl occur. This procedure will be explained at the beginning of the study. Medication adjustments will be guided by the researcher coordinator ([name]). Drug accountability will be assessed at each follow-up visit.

### Maximal exercise and submaximal exercise tests

A maximal exercise test will be performed to determine peak oxygen consumption (VO_2peak_) and ventilatory thresholds. Exercise capacity will be defined by a progressive maximal exercise test performed on a cycle ergometer, with increments of 20 W/min. The test will be carried out at 60 rpm until exhaustion. Oxygen consumption (VO_2_) and carbon dioxide production (VCO_2_) will be determined by averaging the gas exchange by a computerized system (Oxycon Delta; VIASYS Healthcare GmbH, Jaeger, Germany). The test will be finished when the individual is unable to maintain the 60 rpm speed. The VO_2_ peak is defined as the VO_2_ peak reached at the end of this exercise [13]. Heart rate will be continuously monitored by a 12-lead electrocardiogram (Nihon Kohden Corp., Tokyo, Japan).

The ventilatory thresholds will be determined at the breakpoint between the highest point of the CO_2_ production curve and VO_2_ (V slope), or at the point where the curves of ventilatory equivalent for oxygen (VE/VO_2_) and end tidal oxygen (PETO_2_) reach their respective minimum values and begin to increase. The respiratory compensation point will be determined when the levels of VE/VO_2_ reach their minimum values before they start to rise, and when PETCO_2_ reach their maximum values before these begin to decline [14].

The submaximal exercise tests are designed to simulate a typical aerobic exercise session on a cycle ergometer. The test will last 30 minutes, with an intensity based at 10% under the heart rate at the second threshold, which will be obtained in advance. Each patient will undergo two submaximal exercise tests, which will be performed before and after intervention. Before the test, at 15 minutes, at the end (30 minutes) and 60 minutes after each submaximal exercise test, 20 ml of blood will be collected and the variables described later will be measured, with the exception of HbA1c (measured just before exercise). The cardiovascular responses will be obtained as described below.

